#### Sample size estimation

To calculate the minimum sample size for the intervention and control group, we assumed the inter-cluster coefficient to be as low as 0.01. Also, we assumed that 8 clusters (CTCs) would be included in the intervention arm and a similar number in the control arm. We could not find any other studies, based in sub-Saharan Africa, that estimated weight gain after implementing this type of intervention, and therefore we used a similar study conducted in China investigating children in the general population as a reference [21]. In this study, an estimated mean weight gain difference between children of the intervention and control arm was 0.3 kg in six months. To detect the mean difference of 0.3 kg weight gained in the intervention group compared to the control group over a 6-month duration, at a power of 80% and 5% significant level, 24 participants per cluster will be needed. In total, a minimum sample size of 192 participants for each arm will be required to produce the desired effect. To counteract the effect of loss to follow-up, deaths, a number of outcome variables, and missing data, we will attempt to recruit 400 HIV-positive children for the intervention arm and a similar number for the control arm. Therefore, an estimated 800 caregivers will also be recruited to participate in this study, with a similar distribution between the intervention and control groups (400 in each arm).

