#### Feeding frequency

Feeding frequency is also a measure of feeding practices and therefore one of our outcome variables. We will assess the feeding frequency of HIV-positive children by asking the caregivers to recall the number of times they fed their children in the 24 hours preceding the interview. WHO recommends feeding frequency of five times per day for HIV-positive children [19]. We will consider a feeding frequency of below five to be a low feeding frequency.

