### Data analysis

We will analyze the data based on the intention-to-treat principle. We will use both descriptive and regression analyses. For the descriptive analyses, we will conduct both χ^2^ and Student’s *t*-tests to examine the differences in characteristics of participants in the intervention and control groups. This study will have two types of outcome variables. First, nutrition status measured as underweight, wasting, and stunting. Second, feeding practices measured by feeding frequency, dietary diversity, and the quality and quantity of foods consumed. We will use multiple logistic regression analyses to examine the effectiveness of nutrition training on nutrition status and feeding practices of the two arms while adjusting for confounding variables. We will also conduct analyses to see monthly changes in feeding practices and nutrition status and to compare the intervention and control arms. To examine the independent association of nutrition counseling by trained MLPs on outcome variables, we will use repeated measures of ANOVA and Generalized Estimated Equation.

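### Feeding frequency is collected as a count, but the only stated scoring rule is a cut at five and the stated effectiveness test is logistic regression; the plan should say that the count is analysed

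*Protocol article*

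**What the plan says.** Under Feeding frequency, the protocol article measures the outcome by "asking the caregivers to recall the number of times they fed their children in the 24 hours preceding the interview". It then states the basis for a threshold, "WHO recommends feeding frequency of five times per day for HIV-positive children", and gives one scoring rule: "We will consider a feeding frequency of below five to be a low feeding frequency".

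Under Data analysis, feeding frequency is one of several outcomes in the second of two groups: "Second, feeding practices measured by feeding frequency, dietary diversity, and the quality and quantity of foods consumed". The effectiveness test is stated as "We will use multiple logistic regression analyses to examine the effectiveness of nutrition training on nutrition status and feeding practices of the two arms", with adjustment for confounders. Two further statements follow. The first is "We will also conduct analyses to see monthly changes in feeding practices and nutrition status and to compare the intervention and control arms". The second concerns the independent association of counselling by trained providers "on outcome variables, we will use repeated measures of ANOVA and Generalized Estimated Equation". Neither says on what scale feeding frequency enters.

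The Sample size estimation section concerns weight only: "To detect the mean difference of 0.3 kg weight gained in the intervention group compared to the control group over a 6-month duration". Feeding frequency is not designated as primary and does not drive the sample size.

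**The concern.** Multiple logistic regression needs a categorical outcome, and the only categories defined for feeding frequency are below five and five or more. Read together, the scoring rule and the named model make the stated effectiveness test a test of that split.

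In such a test a child who goes from two feeds to four is unchanged, a child who goes from four to five has fully improved, and a child who goes from five to six is again unchanged. If many children sit well below five and gain modestly, a real rise in feeding could give a null result although the count that would show it has been collected. Feeding practices are part of the main objective stated in the Background, so it matters which scale answers the question.

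**Working it through.** **The plan's own figure.** The article states no power or sample size for feeding frequency, so there is nothing to reproduce for this outcome. The 192 per arm is for weight gain and comes without an SD. With 24 per cluster and ICC 0.01, the design effect is 1 + 23 × 0.01 = 1.23 and the effective n is 192 / 1.23 = 156.1 per arm, which implies an SD of about 0.946 kg at two-sided 5% and 80% power. That has no bearing on feeding frequency.

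**Inputs.** From the article: the cut at five, 400 children and 8 clusters per arm (so 400 / 8 = 50 per cluster), and ICC 0.01 (stated for weight; assumed here for feeding). Assumed, because the article gives no distribution: counts follow a rounded normal with control mean 2.5 to 4.5 and SD 0.8 to 1.2.

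**Formula.** Relative efficiency of the split = (z_split / z_count)², at equal n and equal design effect, where
- z_count = (m1 − m0) / √(v0 + v1), with m and v the mean and variance of the count in each arm;
- z_split = (p1 − p0) / √[p0(1 − p0) + p1(1 − p1)], with p the share at five or more.

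**Case A: every child gains about 0.3 feeds.** Control mean 3.0, SD 1.0:
- Count: 0.299 / √(1.080 + 1.082) = 0.2036.
- Split: the share at five or more goes from 6.7% to 11.5%, so 0.0483 / √(0.0623 + 0.1019) = 0.1191.
- Relative efficiency: (0.1191 / 0.2036)² = 0.34.

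| Control mean | SD 0.8 | SD 1.0 | SD 1.2 |
|---|---|---|---|
| 2.5 | 0.08 | 0.18 | 0.28 |
| 3.0 | 0.23 | 0.34 | 0.42 |
| 3.5 | 0.47 | 0.53 | 0.56 |
| 4.0 | 0.68 | 0.66 | 0.66 |
| 4.5 | 0.72 | 0.69 | 0.67 |

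With 400 per arm, the design effect is 1 + 49 × 0.01 = 1.49 and the effective n is 400 / 1.49 = 268 per arm. At SD 1.0, power is about 92% for the count. For the split it is about 49% at control mean 3.0, rising to 79% at 4.5.

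**Case B: 20% of the children below five move to exactly five.** Control mean 3.0, SD 1.0:
- Count: the mean goes from 3.001 to 3.402, so 0.401 / √(1.080 + 1.509) = 0.249.
- Split: the share at five or more goes from 6.7% to 25.3%, so 0.187 / √(0.0623 + 0.1892) = 0.372.
- Relative efficiency: (0.372 / 0.249)² = 2.23.

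Over control means 3.0 to 4.5 at SD 1.0 the ratio is about 1.9 to 2.3 in favour of the split. If only children at four move to five, it exceeds 4.

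**Reading the two cases together.** A uniform rise favours the count at every mean and SD tried. Movement to the target favours the split. The article gives neither the distribution nor the expected pattern of change, so it does not settle which case applies.

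**The case against.** The strongest reply is that the article never drops the count. It collects it, labels values below five as low, and then plans monthly-change analyses, repeated measures ANOVA and GEE. Repeated measures ANOVA is a method for quantitative outcomes. The logistic sentence is also generic: it covers dietary diversity, which is defined as a total score with no cut-point, so it cannot be read as fixing the only scale of every outcome.

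This stands in part. A reader might infer that feeding frequency is scored only as a split, and that any improvement away from the cut counts as no effect anywhere in the trial. The text does not support that; it holds for the logistic test alone. What remains is that the article does not say the ANOVA or GEE uses the count. GEE fits binary outcomes equally well, and the same sentence covers the outcome variables in general, which include underweight, wasting and stunting.

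A second reply is that the cut follows a cited recommendation, so the share of children meeting it is a legitimate target for guideline-based training, and change above five may matter less. That is a good reason to keep and compare the proportion. It is not a reason to leave the scale of the other analyses open.

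A third reply is that the loss of information is itself assumed. This stands: Case B reverses the direction. Nor does the article show that the children feed well below five; eligibility does not depend on feeding frequency and no distribution is reported.

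**Conclusion.** The point holds in a limited form. The one scoring rule and the one named effectiveness test together imply a split at five, and that test ignores change that stays below five or occurs above it. Whether any planned analysis uses the count is left unstated.

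The size is conditional. Under a roughly uniform rise of 0.3 feeds, with assumed SD 0.8 to 1.2 and control mean 2.5 to 4.5, the split keeps about 8% to 72% of the information. The lowest values come from the lowest assumed means. A reader might take this to mean that the plan discards most of its information on feeding frequency. The documents do not support that, because both the size and the direction depend on an unstated distribution and pattern of change.

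Feeding frequency is one outcome among several, not primary, and not the basis of the sample size. The change is worth making, but the trial's main sizing does not depend on it.

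**What to change.** In Data analysis, state that the GEE (or a mixed model) for feeding frequency uses the number of feeds in the previous 24 hours, and report the arm difference in mean feeds per day with its 95% CI. Keep the between-arm comparison of the proportion reaching five as the guideline-based companion. Reporting both covers both patterns of change in the working.

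The cost is a change of wording and one more reported effect for a non-primary outcome. No new data are needed, and the threshold itself stays as it is.

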#### Quantity of food and quality of food

Amount and quality of food consumed by a child is again one of the measures of feeding practices and therefore an outcome variable in our study. We will measure food quality (ingredients or composition) and quantity using Tanzania food composition tables [29]. Such food composition tables provide information on calories, protein, vitamins, and essential minerals per 100 g of the local food type.

Adequate energy intake for HIV-positive children with no infections or severe undernutrition is 10% more than the requirement of normal children of the same age [19]. For HIV-positive children with opportunistic infections, energy requirements are 20% to 30% above normal children of the same age [19]. HIV-positive children with severe undernutrition have energy requirements of 50% to 100% above the required energy intake of HIV-negative children of the same age [19]. We will estimate the foods consumed in the previous 24 hours and work out specific ingredients. We will measure the amount consumed using common feeding utensils, such as plates, bowls or cups. We will categorize the diet as being low quantity if the child consumed an amount below the recommended value for that age.

#### Household food insecurity

We will measure household food insecurity using the Household Food Insecurity Access Scale (HFIAS) [30]. This is because food insecurity was associated with both acute and chronic forms of undernutrition among ART-treated HIV-positive children in Tanzania [3]. This scale has nine items on food access experience. Options are ranked from 0 = 'no’, 1 = 'rarely’, 2 = 'sometimes’, and 3 = 'often’. Score ranges from 0 to 27; higher scores reflect more severe food insecurity. The scale can continuously measure food insecurity, or it can be used categorically to identify food secure or insecure households. The recall duration is shorter compared to other scales; HFIAS uses a 30-day recalling period and has been used among the HIV-positive population in Kenya and Uganda [31-36].

### HIV CTC related data

#### HIV clinical stage

Advanced HIV clinical stage is associated with chronic undernutrition in Tanzania [3,20]. Like in the previous studies, we will use WHO clinical staging to determine HIV/AIDS progression. The four-stage classification uses both medical history and physical examination to classify HIV/AIDS progression. The first two clinical HIV stages are regarded as 'early stages’, whereas clinical HIV stages 3 and 4 are regarded as 'advanced stages’ [37]. In this study, we will extract the highest reached WHO clinical stage from the medical file of each child attending the CTC. The CTC staff updates such information on a routine basis with each CTC visit.

#### ART treatment duration

ART halts HIV/AIDS progression for HIV-positive individuals, improves their immunity, reduces opportunistic infections, and improves appetite [38-40]. Thus, it may also serve to ameliorate the worsening of nutrition status among HIV-positive children. ART treatment duration has also been associated with improvement of underweight and stunting [41]. In this study, we will measure the ART treatment duration as months since initiation.

We will check and record the ART regimen used. According to the national guidelines [17], HIV-positive children in Tanzania are typically treated by combination therapy of three ARTs, referred to as 'highly active antiretroviral therapy’. The fixed combination may either be two nucleoside reverse transcriptase inhibitors and a non-nucleoside reverse transcriptase inhibitor, or two nucleoside reverse transcriptase inhibitors and boosted protease inhibitor. Appropriate combinations differ with child age, anemia status, liver enzymes, and side effects. Children aged up to 36 months are given a combination therapy that includes Zidovudine, Lamivudine and Niverapine. Older children receive a combination of Zidovudine, Lamivudine and Efavirenz. If the child was exposed to Nevirapine on prevention of mother-to-child transmission of HIV/AIDS intervention during pregnancy, Niverapine is usually substituted with Lopinavir boosted with Ritonavir. Stavudine is used in place of Zidovudine if the child is diagnosed with anemia.

#### Opportunistic infections

We will also assess the presentation of any common opportunistic infections. Previous studies showed an association of opportunistic infections with undernutrition among children living with HIV/AIDS in Tanzania [3,42], and other countries in sub-Saharan Africa [40,43,44]. Such opportunistic infections include diarrhea, malaria, tuberculosis, upper respiratory tract infections, and oral/esophageal candidiasis. Diarrhea is defined as the presence of three or more watery stools during the previous 24 hours [45]. Malaria is defined as a typical febrile illness characterized by fever, chills and sweating, and evidenced by parasitological examination [46]. We will assess other opportunistic infections based on a medical history and medical records. We will also examine for intestinal helminthes among the children, as it is an important determinant of undernutrition, and in particular micronutrient deficits.

#### Socioeconomic position

We will assess economic status using a weighted wealth index. The index incorporates household durable assets ownership, such as owning a paraffin lamp, television, radio, telephone, flat iron, refrigerator, bicycle, motor car, farm and having electricity; housing and dwelling characteristics including main floor materials, house ownership, fuel for lighting and cooking, type of toilet, source of water, feeding characteristics, and household food satisfaction [2,28]. We will construct dichotomous variables for these items and carry out factor analysis using principle component analysis to reduce such variables into ones that will load as factor 1, which describe the socioeconomic position of the study population. We will use factor loadings as item weights, and sum them to yield the wealth index for each household [47-49]. We will divide the total weighted wealth index score into quartiles to designate levels of economic status.

#### Sociodemographic data

We will adopt other sociodemographic variables pertaining to children and their caregivers from the women and household questionnaires of the Tanzania Demographic and Health Survey [2,28]. Population surveys in Tanzania have already tested and used these variables both in 2005 and 2010. Such variables will include education level, orphanhood, religion, and marital status.

We will measure education level by years spent in school. We will also group religions into the common denominations found in Tanzania [50]. This includes Christians, Moslems, and non-religious. We will group marital status into either currently married or not currently married [2]. We will consider caregivers who are divorced or widowed at the time of data collection as 'not currently married’. We will measure child and caregiver’s ages in months and years, respectively [2,3].

### Data collection

Prior to data collection, we will train research assistants on the data collection and ethical procedures. We will translate the English questionnaire into Swahili and then back-translate it to English using two independent local researchers to check that is retains its original meaning. We will use the Swahili version of the questionnaire for data collection. The trained research assistants will conduct a pre-test for the questionnaire and the interview in the Swahili language. We will collect data from August 2013 and continue to do so monthly for a period of six months. To assess changes in the MLPs knowledge, we will use the questionnaire from the training manual to collect data before and after the nutrition training.

### Data analysis

We will analyze the data based on the intention-to-treat principle. We will use both descriptive and regression analyses. For the descriptive analyses, we will conduct both χ^2^ and Student’s *t*-tests to examine the differences in characteristics of participants in the intervention and control groups. This study will have two types of outcome variables. First, nutrition status measured as underweight, wasting, and stunting. Second, feeding practices measured by feeding frequency, dietary diversity, and the quality and quantity of foods consumed. We will use multiple logistic regression analyses to examine the effectiveness of nutrition training on nutrition status and feeding practices of the two arms while adjusting for confounding variables. We will also conduct analyses to see monthly changes in feeding practices and nutrition status and to compare the intervention and control arms. To examine the independent association of nutrition counseling by trained MLPs on outcome variables, we will use repeated measures of ANOVA and Generalized Estimated Equation.

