### Randomization process

We will use the CTCs as the unit of randomization. A total of 32 CTCs provide care and treatment to about 1,800 HIV-positive children aged 0 to 14 years old in Tanga. We will exclude private CTCs, as well as CTCs with less than 20 HIV-positive children. A total of 16 CTCs in the area are public and have at least 20 HIV-positive children receiving care and/or treatment; they also represent all the districts of the region. Of the 16 CTCs, 4 are from the Tanga urban area; this is due to a high number of CTCs and HIV-positive patients attending them. All CTCs based in district hospitals will be selected in this study because they fulfill the selection criteria. These 16 CTCs will be eligible for the randomization process: a coin toss to assign 8 CTCs to the intervention arm and 8 to the control arm. A person who is not a member of the study research team will conduct the randomization process.

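### CTCs are randomised, but the logistic regression and repeated-measures ANOVA make no stated allowance for CTC and the GEE has no stated clustering unit

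*Protocol article*

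**What the plan says.** All references are to the protocol article.

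- **Randomization process:** "We will use the CTCs as the unit of randomization". A coin toss assigns 8 of the 16 eligible CTCs to each arm.
- **Sample size estimation:** "we assumed the inter-cluster coefficient to be as low as 0.01", and "we assumed that 8 clusters (CTCs) would be included in the intervention arm and a similar number in the control arm". The result is that "at a power of 80% and 5% significant level, 24 participants per cluster will be needed", so "a minimum sample size of 192 participants for each arm will be required". To cover losses and missing data, "we will attempt to recruit 400 HIV-positive children for the intervention arm and a similar number for the control arm".
- **Data analysis:** the effectiveness question goes to one method: "We will use multiple logistic regression analyses to examine the effectiveness of nutrition training on nutrition status and feeding practices of the two arms", adjusted for confounders. For the independent association of counselling by trained providers with the outcomes, "we will use repeated measures of ANOVA and Generalized Estimated Equation". Chi-square and t-tests are named too, but only to describe participant characteristics by arm.

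The Data analysis section mentions no CTC effect, cluster-robust variance or cluster-level summary, and does not say what the GEE is grouped on.

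**The concern.** Children in one CTC share the same providers and the same clinic, and they receive or miss the intervention together. The sample size accepts that their outcomes are correlated. A logistic regression that treats about 800 children as independent does not. Adjusting for child-level confounders does not restore the clinic as the unit of inference. Repeated-measures ANOVA deals with visits within a child, which is a different level of correlation.

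If the plan is followed as written, standard errors are too small, and ordinary differences between clinics can be read as an effect of training. The Discussion says the findings could support scale-up, so a false positive would matter.

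**Working it through.** **1. Inputs from the protocol article.** 8 CTCs per arm; ICC 0.01; 5% significance level (two-sided assumed, since sidedness is not stated); minimum 24 children per CTC; planned 400 per arm, so 400 / 8 = 50 per CTC on average.

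**2. The plan's own figure.** 8 × 24 = 192 per arm is right. The figure of 24 cannot be derived independently, because no standard deviation (SD) of weight gain is given. Working back, the design effect is 1 + 23 × 0.01 = 1.23 and the effective size is 192 / 1.23 = 156.1 per arm. The implied SD is 0.3 / [(1.960 + 0.842) × √(2 / 156.1)] = 0.95 kg; after rounding up to whole children, 0.93 to 0.95 kg gives 24. So 24 is consistent with a sample size that allows for clustering.

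**3. False-positive rate if CTC is ignored.** With equal cluster sizes m, the design effect is DE = 1 + (m − 1) × ICC, and the true rate of a nominal 5% test is 2 × [1 − Φ(1.96 / √DE)].

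- m = 50, ICC 0.01: DE = 1 + 49 × 0.01 = 1.49; 1.96 / 1.221 = 1.606; rate 10.8%.
- m = 24, ICC 0.01: DE = 1.23; 1.96 / 1.109 = 1.767; rate 7.7%.

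| ICC | m | DE | Rate | Multiple of 5% | Simulated logistic test |
|---|---|---|---|---|---|
| 0.01 (protocol) | 24 | 1.23 | 7.7% | 1.5 | 7.4% |
| 0.01 (protocol) | 50 | 1.49 | 10.8% | 2.2 | 11.0% |
| 0.02 (assumed) | 24 | 1.46 | 10.5% | 2.1 | 10.5% |
| 0.02 (assumed) | 50 | 1.98 | 16.4% | 3.3 | 16.6% |
| 0.05 (assumed) | 24 | 2.15 | 18.1% | 3.6 | 18.6% |
| 0.05 (assumed) | 50 | 3.45 | 29.1% | 5.8 | 29.3% |

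The last column comes from 20,000 simulated null trials per row, with 8 CTCs per arm, a beta-binomial outcome and an assumed prevalence of 30%.

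**4. Repeated-measures ANOVA.** The between-arm test was simulated on child means over six visits (4,000 null trials; continuous outcome; assumed within-child correlation 0.7). At ICC 0.01 it rejected in 8.6% of trials with 24 per CTC and 11.9% with 50. Modelling the visits within a child does not remove the clinic-level error.

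**5. Methods that respect the CTC.** In the logistic simulations, a t-test on CTC proportions with 14 degrees of freedom rejected in 4.7% to 5.0% of trials. A GEE clustered on CTC, but with an uncorrected sandwich variance, rejected in 8.5% to 8.9%.

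**The case against.** The strongest reply is that GEE is in the plan. Counselling by trained providers is how the intervention reaches the children, so the GEE is an analysis of the intervention effect. Grouped on CTC, it would address the clustering. This is also a condensed article, and working correlation, variance estimator and degrees of freedom normally belong in an analysis plan that is not shown. Much of this stands: the GEE's clustering unit is unstated, which is not the same as wrong. It does not rescue the logistic regression, which the text itself ties to the effectiveness question. A GEE mentioned after the monthly comparisons could equally be grouped on the child.

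A reader might infer more than the article supports:

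- **Effectiveness is also tested by chi-square and t-tests.** The article gives these to participant characteristics only.
- **The ANOVA will be run on binary underweight, wasting and stunting, or will discard every child with a missed visit.** The article fixes neither. It also yields z-scores, a diversity score and a feeding count, and it does not describe the handling of missing data.
- **The GEE will use an uncorrected sandwich variance.** The article names no variance estimator. The simulation in step 5 is a reason to specify a correction, not evidence of an error in the plan.

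**Conclusion.** The point holds. The plan randomises and sizes by CTC, then assigns effectiveness to a child-level method with no stated allowance for CTC. The repeated-measures ANOVA has the same gap, and the GEE's clustering unit is open.

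On the protocol's own figures, ignoring CTC gives a false-positive rate of about 11% at 50 children per CTC and about 8% at 24, or 2.2 and 1.5 times nominal. It is tempting to say that error rates are up to six times nominal, but the article does not support that. Six times needs an ICC of about 0.053 at 50 per CTC, or 0.112 at 24, and the only ICC given is 0.01. The 29% figure is a what-if at an assumed ICC of 0.05.

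The figures assume a two-sided test and equal CTC sizes; unequal sizes would raise the rates somewhat. They also carry the ICC of 0.01, set for weight gain, over to the nutrition and feeding outcomes, for which the article gives none. If confounder adjustment absorbed some between-CTC variation, the inflation would be smaller.

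**What to change.** State in the Data analysis section that every between-arm comparison of outcomes accounts for CTC, and name the method for each outcome before the data are analysed. Any of these would do:

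- a mixed model (linear, logistic or count, as the outcome needs) with a random effect for CTC, and one for child where monthly visits are used, with a small-sample correction and about 14 degrees of freedom;
- GEE with CTC as the clustering unit, a small-sample-corrected variance and a t reference on about 14 degrees of freedom;
- a t-test on CTC-level summaries with 14 degrees of freedom (16 CTCs − 2 arms).

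The small-sample provision is needed because there are only 16 clusters. Do not base the effectiveness conclusion on a logistic regression or ANOVA that ignores CTC. The descriptive comparisons of participant characteristics can stay.

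The cost is a change of wording in the analysis section. Confidence intervals will be wider, but correct. Neither the design nor data collection changes.

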#### Baseline

We will assess nutrition status and feeding practices (feeding frequency, dietary diversity, quality and quantity of food items consumed in the previous 24 hours) of the recruited children. We will investigate the burden of disease caused by opportunistic infections, diarrhea, malaria, and intestinal helminthes. We will also assess MLPs’ nutrition knowledge and skills for managing undernutrition in children living with HIV/AIDS before and after the training.

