#### Follow-up

We will follow-up both intervention and control groups for 6 months. We will evaluate feeding practices, such as feeding frequency, dietary diversity, and quality and quantity of food eaten by children, as well as nutrition status, on a monthly basis for six months. For the intervention arm, we will also measure nutrition knowledge of MLPs before the training, immediately after the nutrition training, and again after the six-month observation period in order to measure the degree of knowledge decay.

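### Each outcome is measured at baseline, but no analysis gives that value a stated role; naming it as a covariate would raise power at no cost

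*Protocol article*

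**What the plan says.** Under Baseline, the article states "We will assess nutrition status and feeding practices" for the recruited children. Under Follow-up, both arms are then measured monthly for six months.

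Under Data analysis, effectiveness is assessed as follows: "We will use multiple logistic regression analyses to examine the effectiveness of nutrition training on nutrition status and feeding practices of the two arms". The adjustment made in that model is described only as "while adjusting for confounding variables". No list of these variables is given, and the baseline value of the outcome is neither included nor excluded. The same section adds "We will also conduct analyses to see monthly changes in feeding practices and nutrition status and to compare the intervention and control arms", and for the independent association of counselling with the outcomes, "we will use repeated measures of ANOVA and Generalized Estimated Equation". None of these sentences says whether the baseline measurement enters as a covariate, as the first of the repeated outcomes, or as the value subtracted to form a change.

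Chi-square and t-tests are also planned "to examine the differences in characteristics of participants in the intervention and control groups"; they are described as descriptive.

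Under Randomization process, 16 clinics are allocated 8 to 8 by coin toss, and no stratification or matching is described. Under Sample size estimation, the trial is sized on a 0.3 kg difference in six-month weight gain.

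**The concern.** A child's own baseline value is likely to be among the best predictors of that child's status six months later. If it is left out of the effectiveness model, two things follow. Stable differences between children stay in the comparison and cost power. And with only eight clinics per arm, a chance difference at baseline carries into the follow-up comparison in proportion to the baseline-to-follow-up correlation.

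The sizing and the effect model also differ. Weight gain already subtracts baseline, whereas a logistic regression on underweight, wasting or stunting does not unless baseline is added.

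A smaller point is timing. The article does not say at which visit the adjustment variables are taken. Clinical stage, for example, is read from a medical file of which it says "The CTC staff updates such information on a routine basis with each CTC visit". A covariate read after training has begun could itself have been changed by the intervention.

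**Working it through.** **1. The plan's own figure.** Inputs from Sample size estimation: difference 0.3 kg, intracluster correlation 0.01, 8 clinics per arm, 24 children per clinic, 80% power, 5% level (two-sided assumed).

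- Total: 8 × 24 = 192 per arm, as stated.
- Design effect: 1 + (24 − 1) × 0.01 = 1.23. Effective number per arm: 192 / 1.23 = 156.1.
- No standard deviation is given, so the figure cannot be reproduced independently. Solving for it: SD = 0.3 × √(156.1 / 2) / (1.960 + 0.842) ≈ 0.946 kg. The stated size is consistent with that SD and is not shown to be wrong.

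**2. Chance difference at baseline.** Inputs: 400 children per arm, so 400 / 8 = 50 per clinic; intracluster correlation 0.01; stunting 49% (Study area: under-fives in the Tanga general population, used only as a proxy).

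- Design effect: 1 + 49 × 0.01 = 1.49.
- SD of the arm difference: √(2 × 1.49 / 400) = 0.086 SD units.
- For stunting: 0.086 × √(0.49 × 0.51) = 4.3 percentage points. The chance of a gap above 5 points is about 25%.
- With an assumed intracluster correlation of 0.05, the design effect is 3.45, the SD is 0.131 SD units or 6.6 points, and the chance is about 45%.

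**3. Effect on the logistic model.** Simulation of 16 clinics of 50 children, intracluster correlation 0.01 with the same clinic effect at both times, 49% stunted at baseline, and a latent shift of 0.25 SD in the intervention arm (assumed). The child-level correlation r between baseline and follow-up is also assumed. Standard errors were cluster-robust, the critical value came from t on 14 degrees of freedom, and there were 400 replicates per row.

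| r | Power, no baseline | Power, baseline status (yes/no) | Power, baseline score (continuous) |
|---|---|---|---|
| 0.5 | 62% | 74% | 79% |
| 0.7 | 67% | 83% | 90% |
| 0.9 | 65% | 97% | 98% |

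The Monte Carlo error at 62% is √(0.62 × 0.38 / 400) ≈ 2.4 points, which accounts for the spread in the first power column. With no shift, the models without baseline and with baseline status rejected at similar rates (7.5% and 7.2% at r = 0.5, 5.2% and 4.8% at r = 0.7, 5.0% and 5.8% at r = 0.9). The gain is therefore not bought with false positives.

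At r = 0.7 the log odds ratio moved from −0.40 to −0.54 when baseline status was added, while its empirical standard deviation went from 0.158 to 0.166. In this model the gain comes from a larger conditional estimate, not from a smaller standard error.

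**4. Against an analysis of change.** For a continuous outcome with equal variance at both times, baseline adjustment multiplies the variance of a change analysis by (1 − r²) / [2(1 − r)] = (1 + r) / 2.

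- r = 0.5: factor 0.75. Power at 192 per arm: Φ(2.802 / √0.75 − 1.960) = Φ(1.275) ≈ 90%.
- r = 0.7: factor 0.85. Φ(2.802 / √0.85 − 1.960) = Φ(1.079) ≈ 86%.
- r = 0.9: factor 0.95. Φ(2.802 / √0.95 − 1.960) = Φ(0.915) ≈ 82%.

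Each is compared with the planned 80%.

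**The case against.** The strongest reply is that this is a condensed article. The covariate set is open, a fuller plan may name the baseline value, and the analysis of monthly change, the repeated-measures ANOVA and the estimating equations may already use it. That stands as far as it goes. It limits the point to a role left undefined, and it makes the smaller gain in step 4 the relevant one wherever change is what is analysed.

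Some stronger readings are tempting, and the document does not support them:

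- **That baseline is deliberately left out in favour of other variables.** The text excludes nothing.
- **That the plan adjusts for clinical stage, treatment duration, infections, food insecurity and economic position.** These are described as measurements; nowhere are they listed as model covariates.
- **That part of the effect will be adjusted away through later values.** The article never says that time-updated values enter a model, and infections, diarrhoea, malaria and helminths are listed under Baseline.
- **That the chi-square and t-tests choose the covariates.** They are called descriptive.
- **That the linear-model factor 1 − r² measures the loss.** It compares an adjusted with an unadjusted follow-up value of a continuous outcome. It fits neither a logistic model nor a change analysis.
- **That chance imbalance biases the estimate.** Over repeated randomisations it does not; it adds variance and can distort the one allocation that is made.

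What survives is that the article does name its effectiveness model and its basis for adjustment, and that basis gives the most useful available covariate no place.

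**Conclusion.** The point holds as a free improvement. Baseline values of every outcome are collected, no analysis in the article states what is done with them, and 16 coin-tossed clinics leave a chance baseline difference that is not negligible: about 0.09 SD, or 4.3 points for stunting, at the plan's intracluster correlation.

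In the logistic model, power rose at every correlation tried, from about 62–67% to 74–97% with baseline status. Against a change analysis it rises from 80% to about 82–90%, and the benefit shrinks as the correlation grows.

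The power figures rest on assumed correlations of 0.5–0.9, and the logistic ones also on an assumed 0.25 SD shift. The 4.3 points rest on a prevalence borrowed from general-population under-fives. The direction does not depend on the exact values within these ranges; the size does.

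**What to change.** In Data analysis, state for the cluster-aware effect model that the baseline value of the same outcome is a prespecified covariate (the continuous score where there is one, otherwise baseline status), together with age and sex. State that any further covariate is named in advance and taken from the baseline visit only. Say what role the baseline measurement has in the change, repeated-measures and estimating-equation analyses. Where the model is logistic, note that the odds ratio is conditional on baseline.

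The cost is a few sentences. The baseline outcomes are already due to be collected, so no visit, measurement or child is added.
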